### Who will take informed consent? {26a}

All participants will sign informed consents after an accurate explanation of the process by the physician ([name])

### Additional consent provisions for collection and use of participant data and biological specimens {26b}

N/a. All necessary items have been mentioned in the main informed consent, and there is not any ancillary study.

### Interventions

#### Explanation for the choice of comparators {6b}

Autologous skin transplantation or conventional treatment with Vaseline gauze and antibiotics have been considered as comparators due to the fact that these therapeutic methods are the most common standard treatments.

#### Intervention description {11a}

In the first phase of the study, following initial resuscitation, patients will receive allogenic transplantation within the first 5–10 days after the injury. After preparing the patient for the surgery and through general anesthesia in the operating room of Shahid Motahari Hospital, Tehran, Iran, debridement of the necrotic tissues will be conducted by the tangential method. After that, an adrenaline-soaked gauze will be placed on the wound site for 3–5 min to control the bleeding. After preparing the underlying condition, a 2nd-degree burn wound with a maximum area of 60 cm^2^ will be selected and will be covered by an allogeneic keratinocyte sheet. In the second phase of this project, the same procedure will be conducted; however, based on the randomization list, three separate wounds of a single patient will be selected, and allogeneic keratinocyte sheet transplantation, autologous skin transplantation, or conventional treatment will be selected for each wound. Encountering any serious adverse events (SAEs), the second transplantation of the keratinocyte sheet will not be administrated and the patient who experienced SAEs will receive conventional treatment. Figure 1 provides a flow diagram for phases I and II of this protocol. In addition, the SPIRIT flowcharts of the study are presented in Figs. 2 and 3.

**Fig. 1 Fig1:**
[figure not shown]
Patients flow diagram phase I and II

**Fig. 2 Fig2:**
[figure not shown]
SPIRIT flowchart of phase I

**Fig. 3 Fig3:**
[figure not shown]
SPIRIT flowchart of phase II

#### Criteria for discontinuing or modifying allocated interventions {11b}

Once any reports of SAEs related to the product transplantation are documented, this trial will be terminated.

#### Strategies to improve adherence to interventions {11c}

The patients will be monitored by regular follow-ups on days 3, 7, 10, 14, 21, and 28, after the transplantation. In addition, in the 3rd and 6th month after the transplantation, we will also have additional follow-up sessions which could provide an excellent adherence to the intervention.

#### Relevant concomitant care permitted or prohibited during the trial {11d}

During the study, the patients are allowed to use medications such as non-steroidal anti-inflammatory drugs (NSAIDs) for symptom alleviation.

#### Provisions for post-trial care {30}

N/a. There is no ancillary study and post-trial care. The patients in phases 1 and 2 will be followed up for 6 months after the first transplantation.

### Outcomes {12}

The primary endpoint for this study is safety, which will be evaluated in all follow-ups by Common Terminology Criteria for Adverse Event (CTCAE), version 5.0 [27]. Furthermore, secondary endpoints of this project are time to wound epithelialization, skin graft take rate, scar assessment, wound closure, and quality of skin structure.

#### Participant timeline {13}

The study timeline for phases I and II are presented in Figs. 4 and 5, respectively.

**Fig. 4 Fig4:**
[figure not shown]
Follow-up timeline of the phase I study

**Fig. 5 Fig5:**
[figure not shown]
Follow-up timeline of the phase II study

#### Sample size {14}

To determine the necessary sample size for the study comparing the response rate between the control group and the intervention group, the formula for duplicate sizes in the two groups was used. It was assumed that four rounds of transplantation would be performed, with a mean correlation of 0.5 between repetitive interpersonal measures, a 5% first type of error, a statistical power of 95%, and a minimum difference in response rate of 45% based on similar studies [26–29]. Using these parameters, a sample size of 40 patients was estimated. In the first phase of the study, 5 patients will be included and in the second phase, and 35 patients will be enrolled based on the approved inclusion and exclusion criteria.$$n=\frac{{2\left( z_{\alpha/2}+ z_{\beta }\right)}^{2}{\sigma }^{2}\left\{1+\left(m-1\right)\rho \right\}}{{md}^{2}}$$

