### Data collection and management

#### Plans for assessment and collection of outcomes {18a}

Patients will be followed up on days 3, 7, 10, 14, 21, and 28, after the transplantation. In addition, in the 3rd and 6th months after the transplantation, we will also have additional follow-up sessions. In each follow-up session, a photo of the patient’s wound will be taken. The degree of epithelialization will be evaluated in each follow-up session through photography by the ImageJ software and at least three repetitive images for each wound will be taken. The skin graft take rate will be assessed on the 10th-day visit, and in the context of < 50% graft take, the allogenic transplantation will be repeated. In the 3rd and 6th month follow-ups, the scar and wound closure assessment will be conducted based on the Vancouver Scar Scale (VSS) and the Patient and Observer Scar Assessment Scale (POSAS).

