### Interim analyses {21b}

In phase I, P2–P5 will receive a keratinocyte sheet with a 1-month interval after P1 for safety considerations. Moreover, all participants in phase I and II will be monitored at 3, 7, 10, 14, 21, and 28 days and 3 and 6 months after transplantation by consideration of any probable AEs and SAEs, and wound observation by the investigator. After the completion of the phase I clinical trial, all data includes AEs and SAEs, and wound healing process will be assessed and reviewed to confirm the safety of the process for starting the next phase. After the completion of the phase II clinical trial, all data from both phases will be analyzed.

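### The basis given for 40 patients at 95% power is a two-independent-group, four-round calculation that counts 5 non-randomised patients, whereas phase II compares three wounds within each of 35 patients

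*Protocol article*

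**What the plan says.** The Sample size section describes the calculation as "comparing the response rate between the control group and the intervention group, the formula for duplicate sizes in the two groups was used". It adds "It was assumed that four rounds of transplantation would be performed, with a mean correlation of 0.5 between repetitive interpersonal measures", a 5% type I error, 95% power and a 45-point minimum difference in response rate. The result, 40 patients, is divided into 5 for phase I and 35 for phase II. The variance put into the formula is not given.

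The design sections describe something else:

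- **Phase II comparison.** Under Intervention description, "three separate wounds of a single patient will be selected". Sequence generation allocates the wounds 1:1:1 to autograft, conventional treatment or keratinocyte sheet. Every patient is therefore his or her own control.
- **Number of transplantations.** Plans for assessment and collection of outcomes describes a day-10 check of graft take after which, "in the context of < 50% graft take, the allogenic transplantation will be repeated". Intervention description mentions a second sheet transplantation and no later one.
- **Phase I.** The abstract and Trial design call it a separate, non-randomised trial. Eligibility asks for only one wound.
- **Analysis.** Statistical methods names a Student t-test or chi-square test for the phase II group comparison. Interim analyses says that, once phase II is complete, "all data from both phases will be analyzed".

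**The concern.** The stated sample size and the described trial differ on three counts: separate groups against wounds within a patient, four repeated outcomes against one transplantation with a conditional repeat, and 40 patients against the 35 who are randomised.

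This is the only justification for enrolment in the document. If its model is not the trial's model, the 95% is not tied to the comparison that will be made. Nor can a reader tell which contrast is powered, since there are two comparators, or at what alpha. This is more than detail left to an analysis plan, because the section prints a formula, inputs and a result that conflict with the design.

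**Working it through.** **Inputs.** From the Sample size section: two-sided alpha 0.05 (the formula uses z for alpha/2), power 0.95, m = 4, rho = 0.5, d = 0.45. Assumed: variance 0.25, the maximum for a proportion. The correlation between wounds of one patient is not given, so I use 0 to 0.5.

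**1. Reproducing the 40.** (1.960 + 1.645)² = 12.995.

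n = 2 × 12.995 × 0.25 × (1 + 3 × 0.5) / (4 × 0.45²) = 16.243 / 0.81 = 20.05 per group, or 40.1 for two groups.

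Reading 40 as the size of each group would need a variance of about 0.50, which a proportion cannot have. So 40 is the sum of two separate groups of about 20. With a pooled variance for control rates of 10% to 50%, the total ranges from 32.0 to 40.1.

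**2. Removing phase I, keeping the printed model.** 35 patients are 17.5 per group. Standard error = √(2 × 0.25 × 2.5 / (4 × 17.5)) = 0.1336. Then 0.45/0.1336 − 1.960 = 1.41, which is 92.0% power.

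**3. Direction of the correlation.** The printed formula carries {1 + (m − 1)rho}/m, which grows with rho. A contrast of two wounds in the same patient carries (1 − rho), which shrinks with it: n = 2 × 12.995 × 0.25 × (1 − rho) / 0.2025.

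| rho | Printed formula, m = 4, per group | Within-patient contrast, patients |
|---|---|---|
| 0 | 8.0 | 32.1 |
| 0.3 | 15.2 | 22.5 |
| 0.5 | 20.05 | 16.0 |

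The two correlations are also different quantities: one is between repeated measures under the same treatment, the other between differently treated wounds.

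**4. Power of the design as described, paired analysis, 35 patients, 45 points.** At rho = 0 the standard error is √(2 × 0.25 / 35) = 0.1195.

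- One comparison at 5%: 0.45/0.1195 − 1.960 = 1.80, or about 96%. The exact McNemar test at 27.5% against 72.5% gives 95.3%.
- Each of two comparisons at 2.5% (an assumed split): 0.45/0.1195 − 2.241 = 1.52, or 93.6%. Exact McNemar gives 91.0%.
- At rho = 0.3 the figures are about 99% in both cases.

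**5. Difference detectable with 95% power, 35 patients, one comparison at 5%.** d = √(2 × 12.995 × 0.25 × (1 − rho) / 35), which is 0.431 at rho 0, 0.360 at 0.3 and 0.305 at 0.5. These are normal approximations; exact McNemar for 43 points at rho 0 has about 93%.

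**6. Effect of the named test.** An unpaired test uses a standard error of 0.1195 whatever rho is, so it needs an observed difference above 1.960 × 0.1195 = 0.234. At rho = 0.5 the true standard error is 0.1195 × √0.5 = 0.0845. For 30.5 points, (0.305 − 0.234)/0.0845 = 0.83, or about 80% power, not 95%.

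**The case against.** The strongest reply is that nothing is lost in practice: for one comparison, 35 patients serving as their own controls deliver the 95% promised for 45 points. That is right. The defect lies in the derivation, not in the size of the trial. The primary endpoint is safety, which lowers the stakes further.

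Three stronger readings are tempting and are not supported.

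- **A shortfall.** A reader might set m = 1 in the printed formula, obtain 2 × 12.995 × 0.25 / 0.2025 = 32.1 per group, and infer that about 64 patients are needed. That describes a parallel two-group trial, which nobody plans. Here 32.1 is wounds per treatment, and one patient supplies a wound to each, so it means about 33 patients. Phase II has 35.
- **Phase I pooled into the efficacy comparison.** Interim analyses says only that data of both phases will be analysed. Statistical methods confines the group comparison to phase II, and the phases are registered separately. What stands is that the 5 count toward a powered total, so one clarifying sentence is warranted.
- **A plan for exactly one transplantation.** No limit on repeats is stated, and the flow and timeline figures are not shown. It can be said only that the visible text has no counterpart to four rounds and that the sections need reconciling.

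**Conclusion.** The point holds as a mismatch between the sample-size derivation and the design, and it should be corrected. The 40 is reproduced only as two independent groups of about 20 with four repeated measures, and it includes 5 patients outside any randomised comparison. On its own model, the 35 randomised patients give 92%.

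It does not show that the trial is underpowered. On a paired analysis, 35 patients have about 95–96% power for 45 points at zero correlation for one comparison, more with positive correlation, and about 91–94% if alpha is halved for two comparisons. These figures rest on a variance of 0.25, response rates centred on 50% for the exact test, one response per wound, and no loss of patients.

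**What to change.** Keep 35 patients in phase II and rewrite the Sample size paragraph along these lines: *Within-patient comparison with one wound per treatment and one response per wound, based on the 35 randomised phase II patients. With a paired analysis, variance 0.25 and two-sided 5%, 35 patients give about 96% power for a 45-point difference at within-patient correlation 0, and more if it is positive. The difference detectable with 95% power is about 43, 36 or 30 points at correlation 0, 0.3 or 0.5.* The paragraph should:

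- say whether the keratinocyte sheet is tested against conventional treatment, autograft or both, and the alpha for each. If 2.5% each is chosen, quote about 91–94% at correlation 0;
- define response, which is not among the listed endpoints;
- drop the two-group repeated-measures formula.

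In Statistical methods, replace the Student t-test or chi-square for phase II with a paired analysis (paired t-test or McNemar), since the detectable differences at positive correlation depend on it. Reconcile the four rounds with Intervention description and the outcome-assessment section. In Interim analyses, add that phase I patients contribute safety and descriptive data, not the randomised comparison.

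The cost is one rewritten paragraph, one changed test, one added sentence and the reconciliation of the rounds. Enrolment does not change.

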#### Recruitment {15}

Given that Shahid Motahari Hospital serves as a prominent referral center for burn cases in Iran, the considerable volume of patients meeting our specific inclusion criteria is noteworthy. As a result, the process of patient recruitment is anticipated to transpire within the projected timeframe.

### Assignment of interventions: allocation

#### Sequence generation {16a}

In phase I of the study, we will enroll eligible patients who meet the inclusion and exclusion criteria. This will be done through an open-label approach. In phase 2, random allocation software will be used as the method for randomization. By means of random allocation, each patient’s wounds will be assigned to one of the three groups: group A (autograft), group B (conventional treatment), or group C (keratinocyte sheet). This allocation will follow a 1:1:1 ratio and will adhere to a computer-generated randomization schedule that considers specific strata based on the wound site. Various wounds within a single patient will be subjected to this analysis. The investigation will involve a comparative analysis of the safety and efficacy of allogeneic skin grafts in contrast to autograft skin transplantation and conventional treatments, which encompass the use of Vaseline dressings and topical antibiotics.

#### Concealment mechanism {16b}

The mechanism of implementing the allocation sequence is central randomization. In this study, allocation of participants is performed centrally by a designated system (which generates a randomized list for allocation of patients in different groups) not directly involved in the recruitment or assessment of participants. Central randomization was implemented to ensure unbiased allocation of participants to treatment groups.

#### Implementation {16c}

The sequence of allocation will be conducted by an investigator ([name]). Patients’ enrollment will be done by [name] Assignment of patients to the groups will be done by [name]

### Assignment of interventions: blinding

#### Who will be blinded {17a}

N/a: this study is open-label so there is no blinding.

#### Procedure for unblinding if needed {17b}

N/a: this study is open-label so there is no blinding.

### Data collection and management

#### Plans for assessment and collection of outcomes {18a}

Patients will be followed up on days 3, 7, 10, 14, 21, and 28, after the transplantation. In addition, in the 3rd and 6th months after the transplantation, we will also have additional follow-up sessions. In each follow-up session, a photo of the patient’s wound will be taken. The degree of epithelialization will be evaluated in each follow-up session through photography by the ImageJ software and at least three repetitive images for each wound will be taken. The skin graft take rate will be assessed on the 10th-day visit, and in the context of < 50% graft take, the allogenic transplantation will be repeated. In the 3rd and 6th month follow-ups, the scar and wound closure assessment will be conducted based on the Vancouver Scar Scale (VSS) and the Patient and Observer Scar Assessment Scale (POSAS).

#### Plans to promote participant retention and complete follow-up {18b}

##### Retention strategies

The study will implement a comprehensive retention strategy encompassing regular and frequent follow-up sessions. These follow-ups will involve diverse laboratory tests and complimentary visits. In addition, participants will receive written feedback regarding the outcomes of the conducted health screenings.

##### Withdrawal protocols

Participants hold the prerogative to withdraw from the study at their discretion, irrespective of the rationale, and at any juncture. Furthermore, the principal investigator retains the authority to withdraw participants from the study if it is deemed necessary for their safety or if they are unwilling or unable to adhere to the stipulated study protocols. The possibility of participant withdrawal also exists in the event that the study is prematurely terminated by the study sponsor, governmental bodies, or regulatory authorities prior to the planned culmination date. It should be noted that the discontinuation of the study product for any reason does not constitute grounds for withdrawal from the study.

#### Data management {19}

The data will be collected based on a research-made case report form (CRF). The CRF will include study timeline, history of present illness, basic laboratory data, CTCAE form, photographic and graft take rate information, standard questionnaires of VSS and POSAS, and also a form for pathological evaluation for phase one of the study.

#### Confidentiality {27}

All personal information of the patients will be collected and maintained by a dedicated investigator at Royan Institute in order to protect confidentiality.

#### Plans for collection, laboratory evaluation and storage of biological specimens for genetic or molecular analysis in this trial/future use {33}

In the phase 1 clinical study, 6 months after transplantation, a skin biopsy with a 2-mm^2^ diameter will be taken from three areas: areas treated with keratinocyte sheets, areas treated with autograft, and surrounding healthy skin. The samples will be dehydrated by formalin and ethanol, and after being placed in paraffin wax, they will be cut using a microtome with a thickness of 5 µm. Our samples will be stained with hematoxylin and eosin (H & E). The skin texture, skin ultrastructure, including hemidesmosomes, different tissue layers, and cellular infiltration will be assessed through microscopic evaluation. The collagen composition will be visualized by Masson’s Trichrome (MT) staining. In order to check the epithelialization, vascularization, fibrosis, and scarring, the immunohistochemical staining of tumor growth factor-beta (TGF-β) 1 and 3 will be performed. At least three images will be taken from each sample under the microscope. Due to the pathologic report and stored images, the samples will not be stored.

## Statistical methods

### Statistical methods for primary and secondary outcomes {20a}

After enrollment of all patients, the data will be entered into the SPSS software for statistical analysis. Based on the distribution of data, paired sample *t*-test or non-parametric equal (chi-square test) will be used for comparing the difference in before and after sample data. For comparing each group in phase II, a Student *t*-test or chi-square test will be administered. Moreover, to handle missing data, a multiple imputation test will be used.

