# A single-center, open-labeled, randomized, 6-month, parallel-group study to assess the safety and efficacy of allogeneic cultured keratinocyte sheet transplantation for deep second-degree burn wounds: rationale and design of phase I/II clinical trial

**DOI:** 10.1186/s13063-024-08070-4

**Published:** 2024-04-01

**Keywords:** Skin substitute, Burns, Wound closure, Allograft, Keratinocyte

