**Methods:**

Two consecutive clinical trials were designed, one of them is phase I, a non-randomized, open-label trial with 5 patients, and phase II is a randomized and open-label trial with 35 patients. A total number of 40 patients diagnosed with 2nd-degree burn injury will receive allogenic keratinocyte sheet transplantation. The safety and efficacy of allogeneic skin graft with autograft skin transplantation and conventional treatments, including Vaseline dressing and topical antibiotic, will be compared in different wounds of a single patient in phase II. After the transplantation, patients will be followed up on days 3, 7, 10, 14, 21, and 28. In the 3rd and 6th months after the transplantation scar, a wound closure assessment will be conducted based on the Vancouver Scar Scale and the Patient and Observer Scar Assessment Scale.

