### Eligibility criteria {10}

Prior to the commencement of any study procedures, patients are required to sign the written informed consent.

The following are the inclusion criteria:Age between 18 and 70 yearsBoth gendersAcute second-degree burn injuries involving 20–50% of the total body surface area (TBSA)At least one burn injury for phase 1 and three burn injuries for phase 2 with a maximum area of 60 cm^2^ in the trunk or limbs, with intact musculoskeletal tissue

The following are the exclusion criteria:Having underlying diseases which affect wound healing such as cardiovascular disease, diabetes, malnutrition, and hypertensionPregnancy or breastfeedingActive infection, malignancy, or immunosuppressionRespiratory tract injuryHaving additional trauma injury such as fracture or CNS traumaNeed for intensive careUnwillingness to cooperate in the intervention and follow-ups

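### Phase II randomises three wounds within each patient, but the stated treatment comparison uses tests for independent samples: a conservative error that costs precision, and power for differences smaller than planned

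*Protocol article*

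**What the plan says.** Several places in the protocol article describe phase II as a within-patient comparison:

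- The abstract (Methods) says that the treatments "will be compared in different wounds of a single patient in phase II".
- Eligibility criteria {10} ask for "At least one burn injury for phase 1 and three burn injuries for phase 2".
- Intervention description {11a} says that "three separate wounds of a single patient will be selected", with one of the three treatments going to each.
- Sequence generation {16a} allocates 1:1:1 with wound-site strata: "each patient’s wounds will be assigned to one of the three groups: group A (autograft), group B (conventional treatment), or group C (keratinocyte sheet)". It adds: "Various wounds within a single patient will be subjected to this analysis".

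Statistical methods {20a} has one sentence on before/after data, which names the paired t-test and calls chi-square its non-parametric counterpart. The next sentence covers the treatment comparison: "For comparing each group in phase II, a Student *t*-test or chi-square test will be administered". The article names no paired, patient-blocked or clustered method for that comparison. The title calls the trial a "parallel-group study to assess the safety and efficacy".

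**The concern.** Wounds on one patient share age, nutrition, burn severity and systemic care, so their outcomes are likely to be positively correlated. The usual two-sample t-test and Pearson chi-square take the two sets of wounds as unrelated. They therefore leave the covariance out of the variance of the difference. The paired method is named in {20a}, but for before/after data and not for the comparison that the design pairs.

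At stake are the p-values and intervals for keratinocyte sheet against conventional treatment, where Trial design {8} speaks of superiority, and against autograft. Using each patient as their own control is the main statistical gain of this design, and the stated analysis gives it up.

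**Working it through.** **Inputs from the documents.** 35 phase II patients, each with three wounds. From Sample size {14}: 5% type I error (two-sided, from the z term in the formula), 95% power, a 45-point difference in response rate, m = 4, and correlation 0.5 between repeated measures.

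**Assumptions.** σ² is not stated; I use 0.25, the binomial maximum, for both treatments. The wound-to-wound correlation ρ is not stated; I use 0.1 to 0.5. The 0.5 in {14} refers to repeated measures and is only illustrative here.

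**The plan's own figure.** n = 2(1.96 + 1.645)² × 0.25 × {1 + 3 × 0.5} / (4 × 0.45²) = 20.05 per group, or 40.1 for two groups. The stated 40 is reproduced to within rounding, which makes 0.25 a reasonable variance to carry forward.

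**Standard error of a difference between two treatments.**
- Independent-samples test: √(2σ²/n) = √(0.5/35) = 0.1195.
- True value for two wounds in one patient: √(2σ²(1 − ρ)/n), which is 0.1134 at ρ = 0.1, 0.1000 at 0.3 and 0.0845 at 0.5.
- Ratio: 1/√(1 − ρ).

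**True size and power (normal approximation).** The independent test rejects when the difference exceeds 1.96 × 0.1195 = 0.2343 in absolute value. True size is 2·P(Z > 1.96/√(1 − ρ)). Power for a difference d is Φ((d − 0.2343)/SE_true) for the independent test and Φ(d/SE_true − 1.96) for the paired test.

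| ρ | SE ratio | True size of nominal 5% test | Power at 45 points, independent / paired | Power at 25 points, independent / paired |
|---|---|---|---|---|
| 0.1 | 1.05 | 3.9% | 97.1% / 97.8% | 55.5% / 59.7% |
| 0.3 | 1.20 | 1.9% | 98.5% / 99.4% | 56.3% / 70.5% |
| 0.5 | 1.41 | 0.6% | 99.5% / >99.9% | 57.4% / 84.1% |

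For example, at ρ = 0.5 and 25 points: (0.25 − 0.2343)/0.0845 = 0.186, so 57.4%; and 0.25/0.0845 − 1.96 = 0.998, so 84.1%.

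**Checks by simulation, 35 patients.**
- Continuous outcome, difference of 0.5 SD, two-sample t against paired t: power 0.54 / 0.57 at ρ = 0.1, 0.55 / 0.68 at 0.3 and 0.56 / 0.82 at 0.5. The size of the two-sample test was 0.039, 0.020 and 0.007; the paired test stayed at 0.050.
- Binary outcome, Pearson chi-square against McNemar: size 0.005 against 0.043 at correlation 0.50. Power for 50% against 75% was 0.61 against 0.82, where the correlation is 0.44.

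**The case against.** - **The wording does not say independent.** A paired t-test is also a Student t-test, and other sections describe comparison within a patient. That is true, so the reading is an inference. It is the natural one, because {20a} names the paired test separately for before/after data. Pearson chi-square offers no paired reading.
- **The allocation may not be within-patient.** Concealment mechanism {16b} speaks of allocating patients to groups, which fits a parallel-group title. The abstract, {10}, {11a} and {16a} all put the three treatments on wounds of one patient and outweigh it.
- **The error does no harm at the planned effect.** This stands. At 45 points, power is about 97% or more with either test. The 25-point and 0.5 SD differences are not in the documents; they are my illustrations of what could matter for scar scores or the autograft comparison.
- **The affected efficacy outcomes are secondary.** This also stands: the primary endpoint in Outcomes {12} is safety. The protocol still sets out to assess efficacy and superiority to conventional treatment.
- **Two-sample tests on three groups.** A reader might infer that these are wrong in themselves. They are not: pairwise contrasts of keratinocyte sheet with each comparator are legitimate.

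**Conclusion.** The stated analysis does not match the design, and its standard error is wrong at any non-zero wound-to-wound correlation. With positive correlation, intervals are too wide and p-values too large, by the amounts tabulated above. The size rests on a correlation that the documents do not give; at 0.1 the loss is small, at 0.5 substantial.

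Two stronger readings are tempting, and the documents support neither. One is that ignoring the clustering produces false claims of benefit. With one wound per treatment in each patient and positive correlation, the test is conservative, so a significant result would remain credible. The other is that the trial would miss the effect it was sized for; at 45 points it would not. The practical harm is to the precision of every interval and to power for smaller differences. A non-significant result, especially against autograft, could then be misread as similarity.

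**What to change.** Replace the {20a} sentence on phase II with within-patient comparisons, and name keratinocyte sheet against conventional treatment and keratinocyte sheet against autograft as the planned contrasts.

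- **Continuous scores:** linear mixed model with a patient random effect, and treatment and wound site as fixed effects. Simple fallback: paired t-test or Wilcoxon signed-rank test.
- **Binary outcomes:** either GEE clustered on patient, or conditional logistic regression stratified by patient. State which one, since the first gives a marginal and the second a conditional odds ratio. Simple fallback: McNemar test.
- **Time to wound epithelialization:** a time-to-event model stratified by patient or clustered on patient.

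Change parallel-group in the title to within-patient. The cost is wording and analysis only, with no new patients or data.

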### Trial design {8}

Two consecutive clinical trials were designed, one of them is a phase I, non-randomized, open-label trial, and phase II is a randomized and open-label trial. The second phase will be started after the last follow-up of phase I study, if no SAEs related to the transplantation of keratinocyte sheet is reported. In these studies, we will evaluate the safety and efficacy of allogeneic cultured keratinocyte sheet transplantation for healing deep second-degree burn wounds as well as the superiority of this product to conventional treatments.

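### The protocol aims to show superiority to conventional treatment in phase II, but names no endpoint, contrast or time point that decides it

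*Protocol article*

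**What the plan says.** All places are in the protocol article.

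- **Trial design {8}** gives the aims as safety and efficacy, "as well as the superiority of this product to conventional treatments". No outcome is attached to that aim.
- **Outcomes {12}** makes safety the primary endpoint. The "secondary endpoints of this project are time to wound epithelialization, skin graft take rate, scar assessment, wound closure, and quality of skin structure". No order or lead endpoint is given.
- **Sequence generation {16a}** assigns each patient's wounds to "group A (autograft), group B (conventional treatment), or group C (keratinocyte sheet").
- **Plans for assessment {18a}**: "In the 3rd and 6th month follow-ups, the scar and wound closure assessment will be conducted based on the Vancouver Scar Scale (VSS") and POSAS. That makes two scales at two times, with wound closure resting on the same assessment.
- **Statistical methods {20a}**: "For comparing each group in phase II, a Student *t*-test or chi-square test will be administered". The same section reserves the paired t-test for before-and-after data.
- **Sample size {14}** uses "a 5% first type of error" and 95% power for a difference in response rate between one control and one intervention group. Response rate is not among the endpoints in {12}.

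**The concern.** A superiority aim needs one answer to the question of which result would establish it. Here the aim, the endpoint list, the sample size and the analysis each describe something different. The aim names a comparator but no outcome. The list names outcomes but no priority. The sizing uses two groups and an unlisted outcome. The analysis treats all groups and outcomes alike, with a t-test that handles two groups at a time.

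Healing time, month-3 VSS and month-6 POSAS can point in different directions. With no blinding and no pre-named test, superiority can be claimed on whichever is significant. The Discussion links the work to registering the product, so the strength of the efficacy claim matters.

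**Working it through.** **1. The plan's own sample size.** With z(α/2) = 1.960, z(β) = 1.645, m = 4, ρ = 0.5, d = 0.45, and σ² = 0.25 (not given; assumed, the maximum for a binary outcome):

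n = 2(1.960 + 1.645)² × 0.25 × (1 + 3 × 0.5) / (4 × 0.45²) = 2 × 12.99 × 0.25 × 2.5 / 0.81 = 20.05 per group.

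Two groups give 40.1, so the stated 40 is reproduced. The 5% level therefore belongs to one two-sided, two-group comparison of a response rate. It is not attached to any endpoint in {12}.

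**2. Outcomes that can bear on sheet versus conventional.** Time to epithelialization is one. VSS and POSAS at months 3 and 6 are four more, making five. Three outcomes are left out. Wound closure is assessed with the same scar scales. The pathology form and biopsy are described for phase I only ({19}, {33}). Graft take may not apply to a wound that receives no graft. Three pairs of treatments then give 5 × 3 = 15 tests.

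**3. False-positive rate if each test truly holds 5%.** With five independent tests, 1 − 0.95⁵ = 22.6%. Correlated outcomes and shared arms need simulation. The setting was 35 patients with three wounds each, no treatment difference, two-sided 5% tests and 20,000 runs per setting. The between-outcome correlation is assumed, from 0.8 (low end of each range) to 0 (high end).

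| Test and correlation between wounds of one patient | Sheet vs conventional, any false positive | All three pairs, any false positive |
|---|---|---|
| Paired t (any correlation) | 13–23% | 29–48% |
| Unpaired Student t, 0.3 | 6–10% | 14–24% |
| Unpaired Student t, 0.5 | 2–3% | 6–9% |

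With paired tests, a false positive in the sheet's favour against conventional treatment occurs in about 7–12% of trials. The within-wound correlations 0.3 and 0.5 are assumptions. The sample-size section gives 0.5 for repeated measures but does not say it applies between a patient's wounds.

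**4. Why the rows differ.** The unpaired test ignores the positive correlation between wounds of one patient and so overstates the standard error. At 0.5 each single test rejects in only about 0.6% of null trials. That is a by-product of a test that does not fit the design. It disappears when the analysis is made within-patient, and the first row then applies.

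**The case against.** **Silence is not an unadjusted analysis.** A reader might infer that every scale and time point gets its own unadjusted test. The text does not say so. Handling of multiplicity among secondary endpoints is commonly left to an analysis plan, and none is shown. This stands. But the outcome and contrast that carry a stated superiority aim are a protocol decision, and items {8}, {12}, {14} and {20a} are all filled in without making it.

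**No 5% family-wise level was promised.** A reader might infer that the true error is several times a stated 5%. The 5% belongs to the response-rate calculation, and efficacy is formally secondary. This also stands, so the rates above show what an open choice among tests would allow. They do not show a breach of a stated guarantee.

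**The inflation is not assured with the named test.** At a within-patient correlation of 0.5 the unpaired test gives 2–3% for sheet versus conventional, which is below 5%. This stands too, and makes the larger figures conditional on a valid within-patient test or little correlation.

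**The all-pairs figure is wider than the aim.** Superiority is stated only against conventional treatment, so 13–23% is the relevant range, or 7–12% for results favouring the sheet. Counting all five listed endpoints as separate three-way comparisons would overcount, for the reasons in step 2 of the working.

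**Conclusion.** The point holds as a gap in design: no stated test decides the superiority aim, and the only 5% level is tied to an outcome that is not a listed endpoint. This conclusion rests on the text alone and needs no simulation.

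The size is conditional. With valid 5% tests and an open choice among five outcomes, the chance of at least one false positive for sheet versus conventional is about 2.6 to 4.6 times 5% (13/5 to 23/5). With the unpaired test it ranges from below 5% to about 10% for within-patient correlations of 0.5 and 0.3. These figures assume that any significant result may be claimed, and that no adjustment exists in a plan not shown. The protocol should be changed before phase II outcomes are examined.

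**What to change.** In {12} and {20a}:

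1. Name one key efficacy test at two-sided 5%, analysed within patient, of keratinocyte sheet versus conventional treatment. Time to wound epithelialization is the natural candidate. The within-patient analysis is part of the fix, because the 5% level is meaningful only for a test that respects the three-wounds-per-patient design.
2. In {14}, either define the response rate in terms of that endpoint or restate the endpoint on which the trial is sized.
3. Test any further confirmatory outcome, for example one scar scale at month 6, only in a pre-stated fixed sequence: each step at 5%, and only if the step before it is significant. The sponsor should justify the order.
4. Label all other outcomes, time points and contrasts exploratory. Report them as estimates with 95% confidence intervals and no superiority claim.

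Safety stays the primary endpoint.

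The cost is a few sentences and a protocol amendment, with no new patients, visits or data. The downside is that a nominally significant result outside the sequence can no longer be called proof of efficacy. If an analysis plan already fixes a lead test, bringing that statement into the protocol is enough.
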